## **II. Specimen Transport and storage**

The specimens collected during one day will be kept in drying racks inside plastic boxes to allow them to dry without exposure to dust, insects, or humidity. At the end of the day, the cards will be transported to a health facility or coordination site and will be allowed to dry for at least 4 hours in the racks. The cards will be cut into two portions, ensuring one circle in one portion and 2 circles in the other portion (do not cut circles in half). Each card portion should have a unique ID label and a specimen label. The card portions will be placed in independent glassine bags and then stored in a zip-lock bag containing a sachet with 5g of silica gel desiccant (Uline Inc Silica gelpacket, Aldrich Chemical) and a humidity indicator card.

The single specimen bags will be placed in large Ziploc bags with additional desiccant packs to protect from humidity. A study coordinator will check the humidity indicators weekly, and change desiccant packs when needed.

At the end of the sample collection the DBS cards will be shipped to CDC laboratories for testing.

## **III. Specimen testing**

**a. Determination of Poliovirus antibodies**

At the CDC laboratory in Atlanta, determination of neutralizing antibody titers against poliovirus types 1, 2 and 3 in oral fluids and serum will be done using standard micro-neutralization assays adapted for dried blood spots [5]. Briefly, three 6-mm punches will be obtained from a circle in the DBS card, and eluted with Eagles's Minimum Essential Medium and Fetal bovine Serum, for serum extraction. The serum will be aliquoted into 384-well plates that contain certain amounts of wild poliovirus of each of the three serotypes. The principle of the test is that the anti-poliovirus antibodies in a serum sample will bind to the virus and block infection of susceptible cells. Because poliovirus is cytopathic, virus that is not bound by antibody infects and lyses cells. The amount of neutralizing antibody is quantitated as a titer based on the last serum dilution to protect susceptible cell culture wells from poliovirus infection and cytopathic effect. Each test serum is run in triplicate and diluted from 1:8 to 1:1024.

The test takes approximately 7 days to complete from the elution of dried blood spot punches to adding luminescent reagent and reading plates for cytopathic effect. In each run there is a control serum which is pooled from serum samples with high neutralizing antibody titers to each Sabin poliovirus. Due to the size of the wells and accuracy required for liquid handling on the scale that is necessary for 384-well plates, this procedure cannot be performed manually.

A reciprocal titer of  $\geq 8$  indicates the presence of neutralizing antibodies, and is considered protective against poliomyelitis.

**b. Determination of antibodies against other vaccine preventable and parasitic diseases by Multiple Bead Assay (MBA)**Luminex analysis or Multiple Bead Assay

Luminex platforms have been used for years to measure levels of multiple analytes in biological samples. Fluorescent microspheres can be readily conjugated with protein ligands, and the different spectral signatures of the labeled beads permit to include up to 100 distinct antigens in a single assay well for quantitative determinations of bound antibody. Luminex-based antibody assays are generally more sensitive than conventional ELISAs, have a wider dynamic range and are highly reproducible from assay to assay. The CDC laboratory has been developing assays for the determination of antibodies (IgG) against several vaccine preventable, parasitic, and neglected tropical diseases.

The assay in the Luminex testing includes antigens to measure protective antibody levels for tetanus, diphtheria, measles and rubella. Tetanus, diphtheria and rubella thresholds of protection are based on WHO unit value cutoffs and standards [6]. The

measles virus nucleoprotein (MV-N) is an important immune target during measles infection and has shown good potential for use in diagnostics in lieu of whole virus [7].

Antigens to be included for malaria IgG serology testing will include both short and long-term markers for exposure. For lymphatic filariasis three antigens will be used: Wb123, Bm14 and Bm33. Wb123 is specific for *Wuchereria bancrofti* the main causative agents of LF; it is highly expressed in the larval stage transmitted by mosquitos, and could be a marker of ongoing transmission. Bm14 and Bm33 are sensitive markers of any historical exposure [9].

For trachoma, two antigens derived from the causative agent *Chlamydia trachomatis* are validated for use on the MBA, pgp3 and CT694. pCT03 (pgp3) is one of the eight total ORFs on the highly-conserved cryptic plasmid which is rarely found in *Chlamydia pneumonia* isolates. CT694 is a secreted protein and has been found to be involved in pathogenesis. CT694 manipulates host proteins by acting as a T3S-dependent substrate, but its exact function is not known. At the individual level high antibody levels indicate active or previous infection. At the community level, communities with higher trachoma prevalence have higher pgp3 and CT694 antibody responses. Lack of antibody in young children in a community may be indicative of interruption of transmission by MDAs and the SAFE strategy [10].

For yaws, two antigens will be assessed, rp17 which is a sensitive marker of historical infection and TmpA which is a marker of recent or ongoing infection. Yaws is an infectious disease caused by *Treponema pallidum* ssp. *pertenue*, which mainly affects children in rural communities in the humid tropics. WHO has targeted yaws eradication by 2020 and has developed the Morges strategy, which is comprised of mapping the disease at a community level and subsequently treating the entire population of communities where yaws is endemic. The program goals are to interrupt transmission in all countries where the disease is currently endemic and to certify that all previously endemic countries are yaws free. Detection of antibodies against rp17 and TmpA integrated into serosurveillance for other diseases can be used to provide evidence for lack of transmission of yaws following these interventions [11].

#### Methods for DBS elution

A 6-mm punch will be extracted from each circle on the DBS card to obtain approximately 10 µL of dried whole blood. As previously described [8], the filter paper will be eluted overnight in buffer consisting of phosphate-buffered saline (PBS) with Tween 20, polyvinyl alcohol, polyvinylpyrrolidone, and lysate from *Escherichia coli*.

### Multiplex bead assay

After overnight storage at 4°C, the final dilutions, which will represent a serum dilution of approximately 1:400, will be incubated with antigen-coupled beads in a 96-well formatted plate.

Antigen-specific IgG is detected on the coupled beads using biotin-linked monoclonal anti-human IgG and IgG4 antibodies. IgG is quantitatively reported through incubation with streptavidin-linked R-phycoerythrin.

Using a reader compatible with Luminex reagents (e.g., MAGPIX), the median fluorescence intensity (MFI) from duplicate wells will be recorded. Background from a DBS blank is subtracted from the median fluorescent intensity. Positive- and negative-control serum dilutions are also included on each plate to monitor assay performance.

WHO international standards obtained from the National Institute of Biological Standards and Control (NIBSC) will be used to create standard curves to identify MFI cutoffs representing protective levels of IgG for tetanus (TE-3), diphtheria (10/262), and rubella (67/182). Thresholds of protection are based on WHO-defined unit values [12-14]. Measles (MV-N) threshold of protection was defined using ROC curve of samples characterized by plaque reduction neutralization test (the current gold standard for measles protective immunity) run on the multiplex bead assay [CDC unpublished]. Cutoffs for malaria, trachoma, yaws and lymphatic filariasis antigens can be determined using known seronegative specimens from different sources.

Below is a table showing the sensitivity and specificity of the determination of antibodies by MBA against the gold standard, when available.

| Disease              | Pathogen              | Antigen | Gold standard                                 |                      | Specificity                   |                      |
|----------------------|-----------------------|---------|-----------------------------------------------|----------------------|-------------------------------|----------------------|
|                      |                       |         | Positive panel Classification                 | Sensitivity (95% CI) | Negative panel Classification | Specificity (95% CI) |
| Trachoma             | Chlamydia trachomatis | Pgp3    | Amplicor PCR (active infection)               | 91% (62% - 98%)      | Non-endemic population        | 98% (93% - 99%)      |
|                      |                       | Ct694   | Amplicor PCR (active infection)               | 91% (62% - 98%)      | Non-endemic population        | 98% (93% - 99%)      |
| Yaws                 | Treponema palladium   | r-p17   | TPP(H)A+, RPR+ (active infection)             | 100% (97%-100%)      | Non-endemic population        | 100% (98%-100%)      |
|                      |                       | TmPA    | TPP(H)A+, RPR+ (active infection)             | 97% (92%-99%)        | Non-endemic population        | 100% (98%-100%)      |
| Lymphatic Filariasis | Wuchereria bancrofti  | Wb123   | blood smear microfilaria + (active infection) | 82% (71%-90%)        | Non-endemic population        | 100% (96%-100%)      |

|            |                                |                      |                                                               |                  |                                                       |                    |
|------------|--------------------------------|----------------------|---------------------------------------------------------------|------------------|-------------------------------------------------------|--------------------|
|            |                                | Bm14                 | blood smear
microfilaria +
(active infection)           | 95%
(87%-98%) | Non-endemic
population                             | 93%
(86%-98%)   |
|            |                                | Bm33                 | blood smear
microfilaria +
(active infection)           | 94%
(85%-97%) | Non-endemic
population                             | 98%
(92%-99%)   |
| Malaria    | Plasmodium
falciparum       | Pf MSP1-19           | blood smear +
(active infection)                           | 75%
(59%-87%) | Non-endemic
population                             | 100%
(96%-100%) |
|            |                                | Pf CSP               | no data                                                       | no data          | no data                                               | no data            |
|            |                                | Pf LSA1              | no data                                                       | no data          | no data                                               | no data            |
|            |                                | Pf AMA1              | no data                                                       | no data          | no data                                               | no data            |
|            | Plasmodium
ovale            | Po MSP1-42           | no data                                                       | no data          | no data                                               | no data            |
|            | Plasmodium
vivax            | Pv MSP1-19           | blood smear +
(active infection)                           | 94%
(81%-98%) | Non-endemic
population                             | 99%
(94%-100%)  |
| Tetanus    | Clostridium
tetani          | tetanus
toxoid    | Double antigen
ELISA (SSI,
Denmark)*                    | 99%              | Not available                                         | 92%                |
| Measles    | Measles virus                  | MV-N                 | Vero cell toxin
neutralization
assay (DRL, UK)*         | 84%              | Vero cell toxin
neutralization
assay (DRL, UK)* | 95%                |
| Rubella    | Rubella virus                  | whole virus          | Plaque reduction
neutralization test
(PRNT)             | 88%              | Plaque reduction
neutralization
test (PRNT)     | 80%                |
| Diphtheria | Corynebacterium
diphtheriae | diphtheria
toxoid | Enzygnost anti-
rubella IgG ELISA
(Siemens,
Germany) | 97%              | Double antigen
ELISA (SSI,
Denmark)*            | 94%                |

**c. Multiplexed photo-induced electron transfer (PET)-PCR for diagnosis of malaria infection**

Nucleic acid amplification tests (molecular tests), such as PCR-based assays, have been shown to have superior sensitivity and specificity compared to microscopy and rapid diagnostic tests, as they can detect very low levels of malaria parasitaemia. However, the cost and complexity of molecular tests has impeded its worldwide use for epidemiological studies and surveillance studies. Recent PCR assays such as the multiplexed photo-induced electron transfer (PET)-PCR, are less complex and have shown to be as robust and cost-effective compared to the nested PCR [15]. This test will be applied to the DBS collected in this study as a confirmatory test for malaria infection status.

First the DNA will be eluted from dried blood with a dilution buffer. Then the DNA will be extracted from the sample using the QIAamp DNA Mini Kits (QIAGEN, Valencia, CA, USA) as described by the manufacturer.

The samples will be screened using the multiplex PETPCR assay as described by Luchi et al. [16]. Briefly, the amplification of Plasmodium genus (forward and reverse primers and 80 nM of the species specific probes will be prepared. Then the following cycling conditions will be applied: an initial step at 50°C for 2 min, 95°C for 10 min, and 45 cycles of 95°C for 15 sec, and 60°C for 1 min. All assays were performed using the Applied Biosystems 7500 thermocyclers (Life Technologies, Grand Island, NY, USA).

A cut-off CT value of 40 will be used to indicate a positive result, i.e. active malaria infection. These findings will be compared with the IgG and antigen detection serological tests.

## 6. Utilization of Results

The assessment of coverage and immunity will inform about the risk of additional VPD outbreaks in the camps and the threat to spread to the nearby Bangladesh host community. The results of this assessment will benefit the FDMN population by:

- 1) Providing evidence about the remaining immunity gaps among the FDMN population in order to identify VPD risks and target future vaccination efforts, both in the FDMN population as well as the nearby host Bangladesh population;
- 2) Identifying barriers to vaccination in the FDMN population, which, in turn, will help the microplanning of future immunization activities.
- 3) Provide information useful to malaria and parasitic control programs for future activities.

## 7. Facilities (Resources)

All study materials (e.g., backpacks and pens; paper questionnaires; tablets; materials for household line listing, household and child selection; wet weather gear; and, DBS sample collection (e.g., gloves, hand sanitizer, gloves, alcohol swabs, single use lancets, DBS filter paper, sample storage materials) will be provided by the study organizers. Laboratory materials (e.g., reagents, disposable laboratory supplies, laboratory testing equipment, etc.) will be provided by the CDC.

## 8. Flow Chart (time frame)

The timeframe and activities anticipated are outlined below:

| Month and Year      | Activity                                                                         |
|---------------------|----------------------------------------------------------------------------------|
| February–March 2018 | Develop protocol; submit protocol to ethical review                              |
| March 2018          | Hire study team personnel; procure study materials and supplies                  |
| March 2018          | Develop training materials for data and sample collection                        |
| April 2018          | Train study team                                                                 |
| April–May 2018      | Conduct data and sample collection                                               |
| May 2018            | Ship samples to CDC                                                              |
| May–June 2018       | Conduct data analysis; disseminate preliminary findings                          |
| May–August 2018     | Test laboratory samples at CDC; finalize data analysis; disseminate final report |

## 9. Ethical Implications

The proposed assessment is minimal risk and does not present significant concerns regarding ethical treatment of study participants. The proposed assessment has been determined to be non-research by the CDC Center for Global Health Office.

All participants will be asked for consent verbally in Rohingya using a standardized script and consent document (see Annex D). The survey objectives, time for participation (per child, approximately 10 minutes for completing the questionnaire and 2–3 minutes for collection of DBS samples if selected), and risks/benefits of participation will be clearly explained to all the survey participants before enrolling them. Minimal risk is a result of pain or small amount of bleeding at the DBS fingerprick site in children selected for DBS sample collection. No participants will be forced to provide information or DBS samples for the study; all participation will be voluntary.

Personally identifying information will not be retained in the dataset. Any remaining DBS samples will be destroyed following completion of the laboratory testing. The enumerators will be highly committed to the respondents to keep the privacy of survey participants' information and sources of data as well as will make their heartiest endeavor to be unbiased in collecting data.

## 10. Analysis plan

| Household vaccine coverage survey |                                                        |                                                        |                                        |
|-----------------------------------|--------------------------------------------------------|--------------------------------------------------------|----------------------------------------|
| #                                 | Result                                                 | Analysis                                               | Details                                |
| 1                                 | Denominators                                           | n/% visited, enrolled, refused, not present: flowchart | Overall, by camp, day, team, age group |
| 2                                 | Demographics                                           | n/% gender, median/range age                           | Overall, by camp & age group           |
| 3                                 | Relationship to child                                  | n/% by categories                                      | Overall, by camp & age group           |
| 4                                 | Date of arrival (if available)                         | Summarize/bar chart                                    | Compare to dates of campaigns          |
| 5                                 | Vaccine doses                                          | n/% for each antigen, divide by # of children          | Overall, by camp & age group           |
| 6                                 | Campaign participation                                 | n/% for each antigen                                   | Overall, by camp & age group           |
| 7                                 | Reasons for no vaccine, decision maker, who took child | n/% for each category, bar chart                       | Overall, by camp & age group           |
| 9                                 | Vaccines at border entry                               | n/% yes/no                                             | Overall, by camp & age group           |
| 10                                | Vaccines prior to entry                                | n/% by oral, injection, scar                           | Overall, by camp & age group           |
| 11                                | Vaccination card                                       | n/% for each antigen                                   | Overall, by camp & age group           |
| 12                                | Disease (malaria symptoms, measles, diphtheria)        | n/% by disease/symptoms                                | Overall, by camp & age group           |
| 13                                | Map of vaccine coverage                                | GPS points for mapping each coverage of antigens       | By camp & age group                    |
| Dried blood spot collection       |                                                        |                                                        |                                        |

| # | Result               | Analysis                                                | Details                                   |
|---|----------------------|---------------------------------------------------------|-------------------------------------------|
| 1 | Denominators         | n/% pricked, refused, not present, failed:
flowchart | Overall, by camp, day, team,
age group |
| 2 | DBS vaccine immunity | n/% coverage for each antigen,
table/graph           | Overall, by camp & age group              |

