- Vaccination of close contacts of diphtheria cases at 19 fixed sites (January 2018);
- Planning for expansion of routine immunization service delivery to new health facilities in the FDMN settlement areas;
- Additionally, beginning in September, 2017, the following vaccination campaigns have taken place:

| Campaign                                                                         | Target Age         | Target Population | Coverage       | Remarks                                 |
|----------------------------------------------------------------------------------|--------------------|-------------------|----------------|-----------------------------------------|
| 1. MR, bOPV and Vitamin A campaign: 16 September-03 October 2017 (except Friday) |                    |                   |                |                                         |
| • MR                                                                             | 6 mons - <15 years | 122,580           | 135,519 (110%) | Card provided (1 st version) |
| • bOPV                                                                           | 0 - <5 years       | 47,168            | 72,334 (153%)  |                                         |
| • Vit-A                                                                          | 6 mons - <5 years  | 44,000            | 72,064 (164%)  |                                         |
| 2. OCV 1st round Campaign: 10-18 October 2017 (including Friday)                 |                    |                   |                |                                         |
| • OCV                                                                            | >1 year            | 658,371           | 700,487 (106%) | No Card, Soap provided                  |
| 3. OCV 2 nd round Campaign : 04-09 November 2017 (except Friday)      |                    |                   |                |                                         |
| • OCV                                                                            | >1 year - <5 years | 182,317           | 199,472 (109%) | No Card                                 |
| • bOPV                                                                           | 0 - <5 years       | 209,931           | 236,696 (103%) |                                         |

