| Campaign                                                                                                   | Target Age         | Target Population | Coverage       | Remarks                                                   |
|------------------------------------------------------------------------------------------------------------|--------------------|-------------------|----------------|-----------------------------------------------------------|
| 4. Measles and Rubella Mop up campaign: 18 November-05 December2017 (except Friday)                        |                    |                   |                |                                                           |
| MR                                                                                                         | 6 mons - <15 years | 336,943           | 354,982 (105%) | Card provided (2 nd version)                   |
| 5. Penta, PCV, bOPV & Td campaign ( 1st round) : 12 - 31 December 2017 (except Friday)                     |                    |                   |                |                                                           |
| Penta, PCV, bOPV,                                                                                          | 6 weeks - <7years  | 185,533           | 149,962 (81%)  | Card provided (2 nd & 3 rd version) |
| Td                                                                                                         | 7 - < 15 years     | 172,007           | 165,927 (96%)  |                                                           |
| 6. Penta, PCV, bOPV & Td campaign ( 2 nd round) : 27 January – 10 February 2018 (except Friday) |                    |                   |                |                                                           |
| Penta, PCV, bOPV,                                                                                          | 6 weeks - <7years  | 185,516           |                | Card provided (2 nd & 3 rd version) |
| Td                                                                                                         | 7 - < 15 years     | 178,471           |                |                                                           |

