#### Specific objectives

##### Primary

- Determine the proportion of FDMN children aged 6 months–6 years who received 0, 1, 2, or 3 doses of pentavalent vaccine and 0, 1, 2, or 3 doses of OPV in campaigns since August 2017
- Determine the proportion of FDMN children aged 1 year–6 years with protective antibody titers for poliovirus, tetanus, diphtheria, measles, and rubella
- Determine the proportion of FDMN children aged 7 years–14 years who received 0, 1, 2, or 3 doses of Td vaccine in campaigns since August 2017
- Determine the proportion of FDMN children aged 7 years–14 years with protective antibody titers for poliovirus, tetanus, diphtheria, measles, and rubella

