##### Secondary

- Determine the proportion of FDMN children aged 6 months–14 years who received measles/rubella, and OCV doses in campaigns since August 2017
- Determine the proportion of FDMN children aged 7 years–14 years who received 0, 1, 2, or 3 doses of OPV in campaigns since August 2017
- Identify reasons for not being vaccinated in the last pentavalent/Td vaccination campaign among FDMN children aged 6 months–14 years
- Determine the proportion of FDMN children aged 6 months–14 years who received vaccination upon entry into Bangladesh
- Determine the proportion of FDMN children aged 6 months–14 years who received vaccination in Myanmar
- Estimate malaria parasite prevalence in children aged 1 year–14 years
- Estimate prevalence of exposure to neglected tropical diseases (e.g., lymphatic filariasis, trachoma, and yaws) in children aged 1 year–14 years

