## **Data Collection, Management and Analysis Plan**

Data collection will take place in Kutupalong refugee camp over the course of about 1 week, in makeshift and informal settlements over the course of 3–4 weeks, and Nayapara refugee camp over the course of about 1 week.

Data will be collected on tablets (Lenovo). Data will be uploaded daily to a Kobo server to enable remote monitoring of data quality. All teams will carry hard copies of the questionnaires as back-ups in case the tablet fails at any point.

A daily random check of entered data will be conducted by the survey manager. Team leaders with respective program personnel will ensure quality data collection at field level.

Vaccination coverage, seroprevalence and respective 95% confidence intervals will be estimated for 6m–6yr old children and 7–14yr old children using survey methods that account for the cluster design and sampling weights.

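### MR and OCV campaign coverage is divided by all children in the survey-date age band, so children too young for the campaigns can be read as missed children; Td and entry vaccination have smaller or unquantified versions of the same problem

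*Protocol*

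**What the plan says.** In the protocol's section 10 (Analysis plan), row 5 on vaccine doses gives the rule "n/% for each antigen, divide by # of children", reported overall, by camp and by age group. No restriction by age or presence at the time of a campaign is stated.

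The objectives in section 3 point the same way:

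- MR and OCV (secondary): "Determine the proportion of FDMN children aged 6 months–14 years who received measles/rubella, and OCV doses in campaigns since August 2017".
- Td (primary): the proportion of "children aged 7 years–14 years who received 0, 1, 2, or 3 doses of Td vaccine in campaigns" since August 2017.
- Entry vaccination (secondary): the proportion of children aged 6 months–14 years "who received vaccination upon entry into Bangladesh". In the analysis plan this is row 9, a yes/no percentage with no stated denominator.

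The campaign table in section 2 gives target ages and dates:

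- OCV: over 1 year, with the last round on 4–9 November 2017 (that round limited to under 5 years).
- MR: from 6 months, with the last campaign ending on 5 December 2017.
- Td: from 7 years, with round 1 on 12–31 December 2017. Children under 7 were in the Penta target group.

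Row 4 of the analysis plan compares arrival dates with campaign dates, but only where the arrival date is available and without linking it to any denominator.

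**The concern.** A child's age band is fixed on the interview day, about five to six months after the last MR and OCV campaigns. The youngest children in the sample could not have been offered those vaccines, yet they stay in the denominator as unvaccinated.

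The first general objective asks whether the campaigns had their expected effect, and another asks about barriers to vaccination. Both questions concern children who could have been reached. The administrative coverage in the campaign table uses target-age populations, so a survey figure over all children is not comparable with it. A gap between the two would partly reflect birth dates, not missed children, and section 6 intends to use the results to target later vaccination.

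**Working it through.** **Planned denominators (they reproduce).** Enrolled children = households × share with an eligible child × (1 − household non-response) × (1 − child non-response).

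- Each registered camp, either age group: 625 × 0.65 × 0.80 × 0.99 = 321.75.
- Settlements, 6m–6y: 728 × 0.65 × 0.95 × 0.99 = 445.0.
- Settlements, 7–14y: 728 × 0.60 × 0.95 × 0.99 = 410.8.
- Totals from rounded parts: 322 + 322 + 445 = 1,089 and 322 + 322 + 411 = 1,055, as stated.

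**Assumptions.** Ages are uniform within each band. The reference interview date is 1 May 2018. The range runs from 6 April (the day after the training dates) to 31 May. No MR or OCV campaign took place after those listed, and target ages were applied strictly. The 6m–6y band spans 84 − 6 = 78 months, 7–14y spans 96 months, and 6m–14y spans 180 − 6 = 174 months.

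**Formula for MR and OCV.** Never-eligible share = (youngest survey age that was ever eligible − 6) / months in the band.

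| Vaccine | Latest birth date ever eligible | Age on 1 May 2018 | Share of 6m–6y | Range | Share of 6m–14y |
|---|---|---|---|---|---|
| OCV | 9 Nov 2016 | 17.7 months | 11.7/78 = 15.0% | 14–16% | 11.7/174 = 6.7% |
| MR | 5 June 2017 | 10.8 months | 4.8/78 = 6.2% | 5–8% | 4.8/174 = 2.8% |

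**Effect if coverage among eligible children is 95% (illustrative value).**

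- 6m–6y: OCV 95 × (1 − 0.150) = 81%; MR 95 × (1 − 0.062) = 89%.
- 6m–14y: OCV 95 × (1 − 0.067) = 89%; MR 95 × (1 − 0.028) = 92%.

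The planned half-widths for the coverage survey are 5.6 and 6.2 percentage points. In the 6m–6y band the OCV shortfall of about 14 points is more than twice these, and the MR shortfall of about 6 points is of the same size.

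**Td, 7–14y.** Between round 1 (12–31 December 2017) and 1 May 2018 lie 4.6 to 4.0 months. So 4.0/96 = 4.1% to 4.6/96 = 4.8% of the band was under 7 in that round (3–6% over the range of survey dates). With three rounds in all, these children could have at most two Td doses.

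**Entry vaccination.** Section 2 gives an estimated 300,000 earlier arrivals and more than 650,000 since August 2017: 300/950 = 32% of the population. The same share among sampled children is not given.

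**The case against.** The best defence is that the objectives ask what proportion of children now in the camps received doses. For immunity gaps, an infant too young for OCV is still unvaccinated, and the all-children proportion is the right quantity. That stands. A reader might infer that coverage is simply understated by construction, but the documents do not support that: the figure misleads only when read as campaign reach.

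Other stronger readings also fail:

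- **Td diluted by the Penta age band.** The primary objectives confine Td to 7–14y and Penta to 6m–6y, and row 5 is also given by age group. Only an overall row that pooled both bands would dilute Td (1,055/2,144 = 49% in band), and the protocol does not say that it pools them. The effect within the band is a few points, below the planned half-widths. The children concerned can still appear with one or two doses.
- **Row 5 governs entry vaccination.** It does not. The breadth of that denominator comes from the objective.
- **Registered camps show who arrived early.** They supply 1,288 of 2,144 expected interviews (60%), but section 2 says that these camps also grew with the new influx, and the estimates are to be weighted. Camp is not a proxy for arrival date.

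It can also be said that denominators by antigen belong in a separate analysis plan. That is fair for rows that state none, but row 5 does state a rule.

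**Conclusion.** The point holds in limited form. For MR and OCV the stated denominators ignore the protocol's own campaign ages and dates. In the 6m–6y band this lowers apparent campaign reach by a factor of about 0.85 for OCV and 0.94 for MR. Over 6m–14y the factors are about 0.93 and 0.97. These sizes rest on uniform ages, the assumed survey dates and no later campaigns; actual ages and sampling weights could shift them.

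For the primary Td objective, about 4–5% (3–6%) of the band could not have three doses. For entry vaccination the direction is clear but the size cannot be derived. The largest effects are on secondary objectives, so this is not a must-fix.

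A separate wording slip can be corrected at the same time. The data analysis paragraph of section 5 says that coverage and seroprevalence "will be estimated for 6m–6yr old children and 7–14yr old children", whereas blood is taken only from 1 year of age.

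**What to change.** 1. Keep the all-children proportion. Beside it, for each antigen and campaign, report coverage among children within the target age on the campaign dates and, where the arrival date is available, already in Bangladesh.
2. Report Td and Penta only within their own age bands. For children who crossed age 7 between rounds, count any diphtheria-tetanus-containing campaign dose.
3. Report entry vaccination also among children known to have arrived after it began, allowing for Penta, PCV and Td having been added on 23 December 2017.
4. State seroprevalence for 1y–6y in section 5.

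No change to sampling or fieldwork is needed if age is recorded in months or as date of birth; the protocol shows only that age is summarised. The eligible denominators are smaller: for OCV in 6m–6y about 1,089 × 0.85 = 926 children. With the design effect unchanged, half-widths grow by 1/√0.85 = 1.08, so 5.6 and 6.2 points become about 6.1 and 6.7. Arrival dates will be incomplete, so the number of children with a known date should be shown.
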